### Sample size

The sample size was calculated based on the main efficacy indicator (FMA-UE score). We referred to a previous similar study as the basis for estimating the sample size [23]. The means and standard deviations (SDs) of FMA-UE scores in the two groups were 30.41 ± 9.07, 23.00 ± 5.58. The sample size estimation formula is as follows:$$ n=\frac{{\left({Z}_{\upalpha}+{Z}_{\beta}\right)}^2{\sigma}^2}{{\left({u}_r-{u}_c-\varDelta \right)}^2} $$

In this formula, *n* is the required number of each group; Assuming one-sided *α* = 0.025 and one-sided *β* = 0.1; The value of Δ is 10% of the mean of the control group in the previous similar study [24]; The required sample size is 13 in each group; Considering a 20% dropout rate, a total of 32 participants should be recruited (16 per group).

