### Randomization and allocation

Randomization is conducted by an independent investigator who is not involved in the recruitment, assessment, treatment, or data analysis. The randomization sequence is generated by computer-generated random numbers. Thirty-two eligible patients are randomly divided into VRMT group and RAVRMT group in a ratio of 1:1. The assignment of patients is concealed in an opaque, sealed envelope, and cases are numbered by an independent investigator in the order of entry into the group. Before starting an intervention, inform therapists of the patient’s specific number and intervention information in order to obtain the assigned treatment.

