### Statistical analysis

Blind the statistician. The clinical data will be analyzed by SPSS25.0 software. For the measurement data of the obtained data, the normality test is first performed. For the measurement data conforming to the normal distribution, it is expressed as the mean ± standard deviation (x ± s). The paired t test is performed before and after the two groups, and the comparison between the two groups is used Two-way repeated measures analysis of variance (2-way repeated measures ANOVA) test. The non-normally distributed measurement data before and after a group of self-comparison uses the Wilcoxon signed rank test, and comparison between the two groups uses the Mann-Whitney signed rank test. The significance level of the statistical test is set to α = 0.05, and the one-sided test is performed. A data monitoring committee will not be implemented because all participants will be treated and adverse events are expected to be low.

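### The sample size is planned at one-sided α = 0.025 but the analysis section tests at one-sided α = 0.05, twice the planned nominal level for any directional test

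*Protocol article*

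**What the plan says.** The Sample size section bases the calculation on the FMA-UE score and sets the error rates: "Assuming one-sided *α* = 0.025 and one-sided *β* = 0.1". It arrives at 13 per group, and at 32 patients in total after an allowance for dropout.

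The Statistical analysis section sets one level for everything it lists: "The significance level of the statistical test is set to α = 0.05, and the one-sided test is performed". The tests it covers are the paired t test and the Wilcoxon test within groups, and two tests between groups. The main between-group test is described thus: "the comparison between the two groups is used Two-way repeated measures analysis of variance (2-way repeated measures ANOVA) test". The Mann-Whitney test replaces it when data are not normally distributed.

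Both sections state the level and the sidedness explicitly. Nothing in the article reconciles them, and nothing sets a separate level for the primary outcome.

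**The concern.** The two sections give different bars for the same claim. One-sided 0.025 is the conventional two-sided 5% standard looked at in one direction. One-sided 0.05 is the two-sided 10% standard. A one-sided 5% test can be defended if it is planned and justified, but here the planning used the stricter level and the looser one appears without explanation.

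The stake is the reading of a borderline result. With both rules in print, a one-sided p between 0.025 and 0.05 can be called positive by citing one section and negative by citing the other, and the choice could be made after the data are seen. This matters in a 32-patient, single-centre device trial that the article says cannot be double-blind.

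**Working it through.** **Inputs.** From Sample size: α = 0.025 one-sided, β = 0.1, and the previous study's scores ("The means and standard deviations (SDs) of FMA-UE scores in the two groups were 30.41 ± 9.07, 23.00 ± 5.58"), so the difference is 30.41 − 23.00 = 7.41. The margin is defined there too: "The value of Δ is 10% of the mean of the control group in the previous similar study". Taking 23.00 as the control mean, Δ = 2.30. From Statistical analysis: α = 0.05, one-sided. The article does not say which SD serves as σ.

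**Step 1: the plan's own figure.** The article's formula is n = (Zα + Zβ)²σ² / (difference − Δ)². Its stated result is: "The required sample size is 13 in each group". With σ = 5.58 (the smaller SD, assumed) and unrounded z values:

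- α = 0.025: 10.507 × 31.136 / 5.11² = 12.53, rounded up to 13, as stated.
- α = 0.05: 8.564 × 31.136 / 5.11² = 10.21, rounded up to 11.

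A two-sample form using the sum of the variances (9.07² + 5.58² = 113.40) and adding the margin to the difference (9.71) also gives 13:

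- α = 0.025: 10.507 × 113.40 / 9.71² = 12.64, rounded up to 13.
- α = 0.05: 8.564 × 113.40 / 9.71² = 10.30, rounded up to 11.

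The stated 13 is thus consistent with the stated planning level. This is support, not proof, because σ was chosen to return 13. For example, σ = 9.07 with Δ left out gives 12.83 at one-sided 0.05, although that departs from the article's formula. The point does not depend on this step, since the planning level is stated outright.

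**Step 2: the two levels side by side.**

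| Section | Level | Critical z | Two-sided equivalent |
|---|---|---|---|
| Sample size | one-sided 0.025 | 1.960 | 0.05 |
| Statistical analysis | one-sided 0.05 | 1.645 | 0.10 |

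Ratio of nominal levels: 0.05 / 0.025 = 2.

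**Step 3: which tests this reaches.** The Mann-Whitney test and any directional contrast can be run one-sided, so the ratio of 2 applies to them. The usual F test p-value is non-directional. For an effect with one degree of freedom F = t², so reading F at 0.05 leaves about 0.025 in favour of RAVRMT, which is the planned level. The one-sided instruction cannot be applied to the F test as it stands.

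**Step 4: illustration in FMA-UE points.** Assume a two-sample t test against zero with pooled SD √((9.07² + 5.58²)/2) = 7.53. The smallest significant difference is t × 7.53 × √(2/n):

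| n per arm | df | one-sided 0.025 | one-sided 0.05 |
|---|---|---|---|
| 13 | 24 | 6.10 | 5.05 |
| 16 | 30 | 5.44 | 4.52 |

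The threshold falls by about 17% in each row. If Δ = 2.30 were a superiority margin to be exceeded, the thresholds at 13 per arm would instead be 8.40 and 7.35. None of these values is the trial's actual decision rule, because the planned analysis is a repeated measures ANOVA and the outcome is defined as change in score.

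**The case against.** The strongest reply is that the analysis sentence may be a slip for two-sided 0.05, which would match the planning level exactly. That is plausible, and the non-directional F test fits it. But the sentence says one-sided, and an analyst who follows it would compare a one-sided p-value with 0.05. If it is a slip, it still needs correcting.

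A reader might infer that the primary analysis will certainly carry twice the planned false-positive risk. The article does not support that. The main between-group test is an ANOVA, and an F test simply read at 0.05 would not double the error in favour of RAVRMT. The doubling is nominal and is confined to directional tests. This part of the objection stands.

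A reader might also infer that success would rest on half the planned strength of evidence. That does not follow: doubling α doubles a nominal error rate, while the illustrative thresholds move by about 17%.

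Nor can anything be said about the registry entry, which is not among the documents.

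That this is a condensed article with an analysis plan not shown does not excuse the conflict. Both levels are stated here, and no separate plan could agree with both.

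**Conclusion.** The contradiction is explicit and should be corrected before outcome data are analysed. The analysis level as written is twice the planned one (5% against 2.5%, one-sided) for the Mann-Whitney test or a directional contrast, and it is unworkable for the F test named as the main between-group comparison. The factor of 2 follows from the two stated levels and needs no assumption about σ, Δ or the form of the test statistic. The point differences do rest on such assumptions (t test against zero, pooled SD 7.53) and are illustrative only.

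The statement concerns the nominal level of a single test. Multiplicity across time points and the unstated σ are separate matters.

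**What to change.** Replace the sentence on the significance level in the Statistical analysis section with:

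> All statistical tests are two-sided at a significance level of α = 0.05; for the between-group FMA-UE comparison this corresponds to the one-sided 0.025 in favour of RAVRMT assumed in the sample size calculation.

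The replacement has to cover all tests, because the present sentence sets the level for every test in that section; wording limited to FMA-UE would leave the others without one. The stated correspondence holds for a comparison with one degree of freedom, so the claim of superiority should be read from such a contrast and not from an F test that spans several time points.

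Cost: one sentence and a slightly stricter success threshold than the present text allows. The planning level is unchanged, so no extra patients or procedures are needed on this account.

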## Discussion

Mirror therapy is based on the theory of mirror neuron system (MNS) and has been widely used in post-stroke rehabilitation [34]. The MNS refers to the brain regions that activate when an individual performs a specific action and when others are observed performing the same or similar action [35]. The human MNS includes the bilateral posterior inferior frontal gyrus (Broca’s area on the left), the ventral premotor cortex, the inferior parietal lobule (angular/supramarginal gyrus), the posterior superior temporal gyrus (Wernicke’s area on the left) [34]. The bilateral posterior inferior frontal gyrus, the ventral premotor cortex, the inferior parietal lobule are all brain regions involved in motor execution [36]. Mirror therapy can improve upper limb motor dysfunction in stroke patients by activating MNS [12, 13]. Virtual reality is used to improve the “immersion” of patients in the process of mirror therapy and reduce the influence of external interference factors [14].

Robot-assisted therapy (RAT) can provide programmed upper limb task training to simulate normal upper limb functional movements. Robot-assisted programmed task training activates cortical striatum pathways that promote motor control, action selection, and reward [37]. The reward generated by RAT guides motor learning through dopamine secretion [38]. In the treatment of upper limb motor dysfunction in stroke patients, RAT can restore upper limb function by activating motion-related brain networks and reward circuits [17].

RAT and VRMT are both promising treatments for improving upper limb motor dysfunction in stroke patients [39]. Combined application of RAT and VRMT could theoretically activate MNS and reward circuits to a greater extent, but further high-quality research is needed before the RAVRMT robot can be widely used in clinical practice. Therefore, we design a single-center, assessor-blinded, randomized controlled clinical trial to observe if the RAVRMT robot can better improve upper limb motor dysfunction after stroke.

### Limitation

A double-blind design cannot be carried out in this study, which may cause deviations and affect the quality of the trial. However, we blind outcome assessors and statistical analysts to minimize the trial deviations.

### Trial status

Participant recruitment has not started.

## Data Availability

The datasets generated and/or analyzed after completing the current study will be available from the corresponding author by reasonable requests.

## Abbreviations

RAVRMT: Robot-assisted virtual reality mirror therapy
VRMT: Virtual reality mirror therapy
RAT: Robot-assisted therapy
fMRI: Functional magnetic resonance imaging
FMA-UE: Fugl-Meyer motor function assessment-Upper Extremity
SD: Standard deviations
MoCA: Montreal cognitive assessment
ADL: Ability of daily living
QOL: Quality of life
SF-36: Short Form 36-Item Health Survey
VAS: Visual analogue scale
IA: Internet addiction
SSQ: Simulator sickness question
MNS: mirror neuron system
